## Abstract

**Background:**

Hypertension is the predominant risk factor for cardiovascular disease morbidity and mortality, with significant healthcare utilization and expenditure. Pharmaceutical management is habitually adopted; although its long-term effectiveness remains ambiguous, and accompanying adverse effects are disquieting. Peppermint owing to its abundance of menthol and flavonoids, possesses a range of potential hypertensive benefits.

**Rationale:**

Our previous trial has shown that peppermint is able to mediate significant improvements in systolic blood pressure in healthy individuals. But there has yet to be any randomized placebo-controlled studies, examining the efficacy of peppermint supplementation in hypertensive individuals.

**Objective:**

This study proposes a placebo randomized controlled trial, exploring the effects of daily peppermint oil supplementation on outcomes pertinent to hypertensive disease in individuals with pre and stage 1 hypertension.

**Methods and analyses:**

This 20-day, parallel randomized, placebo-controlled trial will recruit 40 individuals, assigned to receive either 100μL per day of either Peppermint oil or a peppermint flavoured placebo. The primary trial outcome will be the between-group difference in systolic blood pressure from baseline to post-intervention. Secondary outcome measurements will be between-group differences in anthropometric, haematological, diastolic blood pressure/ resting heart rate, psychological wellbeing, and sleep efficacy indices. Statistical analysis will be conducted on an intention-to-treat basis using linear mixed effects models to contrast differences in the changes from baseline to 20-days between the two trial arms.

**Ethics and dissemination:**

Ethical approval has been granted by the University of Central Lancashire (*HEALTH 01074*) and the study has formally been registered as a trial (*NCT05561543*). Dissemination of the trial findings will be through publication in a peer-reviewed journal.

**Trial registration:**

ClinicalTrials.gov NCT05561543.

**Ethics:**

HEALTH 01074.

## Introduction

Globally, hypertension is renowned as the leading risk factor for cardiovascular disease morbidity and mortality [1]. High blood pressure ranks first among modifiable risk factors in population attributable to cardiovascular disease aetiology, accounting for the largest proportion of coronary heart disease, heart failure, and stroke events [2]. It is associated with significant societal and economic consequences [3] and also mediates significant productivity loss from disability and premature death [4]. Thus, hypertension is one of the most consequential and remediable threats to the health of individuals and society.

Pharmaceutical intervention is the predominant treatment approach for hypertensive disease, and angiotensin-converting enzyme inhibitors, betablockers, calcium antagonists, diuretics, and lipid-lowering therapies are the most commonly adopted approaches [5]. However, whilst these medications are effective in treating hypertensive disease, their cost-effectiveness has not yet been fully established [6]. Additionally, significant adverse effects continue to be frequently reported, raising concerns about their utilization and patient tolerability [7]. These side effects, in additional to global overreliance of daily prescription medication [8], suggest that natural cost-effective approaches are necessary for the management of cardiometabolic disease [9].

Improved dietary practices are the principal approach for the non-pharmaceutical prevention and management of hypertensive and cardiometabolic diseases [10]. Enhanced intake of fruits and vegetables has definitively been shown to improve hypertensive and cardiometabolic disease symptoms [11]. However, maintaining a habitual dietary pattern high in fruits and vegetables has been shown to be difficult to accomplish [12]; therefore, supplementation potentially represents a more appealing treatment and prevention modality.

Peppermint (Mentha piperita L.) is a recurrent flowering plant that cultivates in western Europe and North America. Peppermint itself is a hybrid amalgamation of both spearmint (Mentha Spicata) and water mint (Mentha Aquatica). The peppermint plant contains a diverse chemical profile, including menthol, flavonoids, menthone, and menthyl acetate [13]. Peppermint possesses a broad range of biological activities, including digestive, choleretic, carminative, antiseptic, antibacterial, antiviral, antispasmodic, antioxidant, anti-inflammatory, myorelaxant, expectorant, analgesic, tonic, and vasodilatory properties [13,14], and has importantly been shown through toxicology analyses to be safe for ingestion [15].

Importantly, owing to its antioxidant, anti-inflammatory, and vasodilatory properties, there is growing speculation that peppermint ingestion may target the mechanisms central to hypertensive pathophysiology, and thus confer significant clinical benefits [16]. To date, only very limited studies have been undertaken exploring the influence of peppermint supplementation on cardiovascular outcomes, with Barbalho et al., [17] showing that twice daily supplementation of peppermint, mediated significant reductions in both low-density lipoproteins (LDL) cholesterol and systolic blood pressure. However, this investigation did not feature a control group, meaning that it cannot conclusively be concluded that the improvements were decisively attributable to peppermint supplementation, as opposed to other external mechanisms. Importantly, Sinclair et al., [16] showed using a placebo randomized controlled trial in healthy individuals, that twice daily peppermint supplement yielded significantly greater reductions in systolic blood pressure, triglycerides and state/ trait anxiety compared to placebo.

### Rationale

At the current time, there has yet to be any randomized placebo-controlled intervention studies, examining the efficacy of peppermint supplementation in hypertensive individuals. Therefore, with previous trials demonstrating a positive effect of peppermint ingestion in healthy individuals, there is potential for a more pronounced effect in individuals with pre and state 1 hypertension. Therefore, further placebo-controlled investigations concerning its influence on outcomes pertinent to hypertension may be of both practical and clinical relevance.

### Aims & objectives

The aim of this trial is to investigate the effects of 20-days of twice daily peppermint supplementation in individuals with pre and state 1 hypertension compared to placebo. The primary objective of this placebo randomized trial is to investigate the effects of peppermint supplementation on systolic blood pressure relative to placebo. Its secondary objectives are to determine whether peppermint supplementation impacts upon other risk factors for hypertensive and cardiometabolic disease.

### Hypotheses

In relation to the primary outcome, peppermint oil will mediate statistically significant reductions in systolic blood pressure compared to placebo. Furthermore, for the secondary outcomes, peppermint oil will produce improvements in other cardiometabolic health parameters compared to placebo.

## Materials and methods

### Study design and setting

This study adheres to the latest guidelines for reporting parallel-group randomized trials [18]. The University of Central Lancashire in the city of Preston in Lancashire, Northwest England, will serve as the location for the trial. In accordance with our previous trial, this research follows a 20-day parallel design, incorporating randomized allocation with a placebo control [16] (Figs 1-2). After screening for eligibility and enrolment, participants will then be randomized at the individual level, using a computer program (Random Allocation Software) undertaken by an independent researcher to either a peppermint or placebo group. A permuted block randomization process will be adopted to ensure equal allocation to each trial arm based on the required sample size. Participants and the data analyst will be unaware of the study-group assignments throughout data collection. Indices, pertinent to hypertension, as described in detail below, will be assessed at baseline and after 20-days (post-intervention). In agreement with previous trials involving hypertensive individuals, the primary outcome measure will be the between-group difference in systolic blood pressure from baseline to post-intervention [16,19]. Secondary outcome measures will be between-group differences in anthropometric, haematological, diastolic blood pressure/ resting heart rate, psychological wellbeing and sleep efficacy indices. All experimental visits will take place in the morning and be undertaken in a ≥ 10-hour fasted state. Participants will also be required to arrive hydrated and to avoid strenuous exercise, alcohol, and nutritional supplements 24 h and caffeine 12 h prior.

**Fig 1 pone.0321986.g001:**
[figure not shown]
SPIRIT schedule of enrolment, interventions, and assessments.

**Fig 2 pone.0321986.g002:**
[figure not shown]
Consort diagram describing the study design.

### Inclusion criteria

Participants will be considered eligible for participation if they (1) are aged from 18–65 years; (2) fulfil the classification of pre-stage 1 hypertension outlined by the American Heart Association with an SBP in the range of 120–139 mmHg [20], (3) are not taking prescribed medicine for blood pressure management, (4) have the ability to complete written questionnaires independently and (6) are able to provide informed consent.

### Exclusion criteria

Exclusion criteria are (1) diagnosed with diabetes mellitus and coronary heart disease; (2) pregnant and lactating women; (3) allergy to peppermint, (4) habitual consumption of peppermint products, (5) regular consumption of antioxidant supplements (5) body mass index (BMI) larger than 40.0 kg/m^2^ and (6) current enrolment in other clinical trials of other external therapies.

### Sample size

Given the lack of randomized trial data in this population specifically for peppermint, a pragmatic a priori sample size calculation was undertaken based on our previous trial involving healthy individuals [16]. In this, we observed Cohen’s *d* = 0.81 for the primary outcome. Therefore, as we anticipate a larger effect of peppermint in individuals with pre and stage 1 hypertension, we pragmatically selected a Cohen’s *d* = 0.85. This effect size, combined with the directional nature of our hypotheses, meant that to achieve *α* = 5% and *β* = 0.80, a total sample size of 36 is necessary. To account for a 10% dropout rate, which was conservatively estimated based on our previous trial [16], we adjusted the total sample size to 40 participants.

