### Statistical analysis

Continuous experimental variables will be presented as mean values along with their corresponding standard deviations. To compare compliance levels between the trial arms, between-group linear mixed effects models will be utilized. In these models, group will be treated as a fixed factor, and random intercepts will be included for participants.

All analyses of the intervention-based data will follow an intention-to-treat approach. To determine the effects of the intervention on all of the outcome measures, differences in the changes from baseline to 20-days between the two trial arms will be examined using linear mixed-effects models with a group modelled as a fixed factor and random intercepts by participants adopted, employing the restricted maximum-likelihood method [16]. For linear mixed models, the mean difference between groups in changes from baseline to 20-days (*b*) and 95% confidence intervals of the difference will be presented. As the experimental questionnaires yield data that are predominantly ordinal in nature, the aforementioned effects of the intervention between trial arms will be examined using Mann-Whitney U tests. Effect sizes will be calculated for the changes from baseline to 20-days between the two groups, using Cohen’s d, in accordance with McGough & Faraone, [39]. Cohen’s *d* values will be interpreted as 0.2 = small, 0.5 = medium, and 0.8 = large [40]. The efficacy of blinding will be assessed using a one-way chi-square (*Χ*^2^) goodness-of-fit test [16]. Chi-square analyses will be calculated using Monte-Carlo simulation to determine probability values. All statistical analyses will be performed using SPSS v29 (IBM Inc., SPSS, Chicago, IL, USA), and statistical significance will be considered at a P ≤ 0.05 level.

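### The sample size assumes a one-sided 5% test, but the analysis section declares none and reports a 95% CI with P ≤ 0.05, so the stated 80% power and the decision rule do not match

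*Protocol article*

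**What the plan says.** The Sample size section starts from the previous trial in healthy people ("we observed Cohen’s *d* = 0.81 for the primary outcome"), expects a larger effect in this population, and so "we pragmatically selected a Cohen’s *d* = 0.85". With a 5% significance level and a target of 80% (printed as β), it concludes that "a total sample size of 36 is necessary", and raises this to 40 for 10% dropout. The only reference to sidedness is in the sentence that gives this result, which opens "This effect size, combined with the directional nature of our hypotheses, meant that to achieve". The Hypotheses section is directional too: it predicts a reduction in systolic blood pressure against placebo.

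The Statistical analysis section compares changes from baseline between the arms with a linear mixed model. For the estimated difference, "95% confidence intervals of the difference will be presented", and for all analyses "statistical significance will be considered at a P ≤ 0.05 level". It mentions no one-sided test, one-sided P value or one-sided bound. No section calls the primary test one-sided or two-sided.

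**The concern.** The sample size calculation appears to use direction to reduce the number required, while the analysis section describes a decision rule that does not use direction. A 95% confidence interval excludes zero exactly when a two-sided 5% test rejects, so interval and sample size belong to different tests.

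Two things are at stake. If the result is judged by the interval, or by a two-sided P value, the trial has less power than it states. If it is judged by a one-sided P value, the P value and the published interval can point in opposite directions on the primary outcome. With the choice left open, it could be made after the data are seen.

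**Working it through.** **Inputs.** From Sample size: d = 0.85 (0.81 observed previously), α = 0.05, target power 0.80, 10% dropout. From Study design and setting: equal allocation. From Statistical analysis: a between-group comparison of changes. With one change score per participant, this is treated as a two-sample t-test.

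**Formula.** With n per arm, T follows a noncentral t distribution with 2n − 2 degrees of freedom and noncentrality d·√(n/2). Power is the probability that T exceeds the critical value (plus a negligible opposite tail for the two-sided test).

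**Step 1: reproduce the plan's figure.** For n = 18, the noncentrality is 0.85 × √9 = 2.55 with 34 degrees of freedom.
- One-sided 5%: critical t = 1.691, power 0.803. With 17 per arm, power is 0.782. So 18 per arm, 36 in total, is the smallest adequate size.
- Dropout: 36 / 0.9 = 40. This also reproduces.
- Two-sided 5%: the smallest adequate size is 23 per arm (power 0.805), 46 in total. The normal approximation gives 22 per arm, 44 in total. Neither is 36.

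The calculation is therefore correct, and it is one-sided.

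**Step 2: power under each reading.**

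| Completers | True d | One-sided 5% | Two-sided 5% |
|---|---|---|---|
| 36 | 0.85 | 0.803 | 0.698 |
| 40 | 0.85 | 0.840 | 0.745 |
| 36 | 0.81 | 0.769 | 0.656 |
| 40 | 0.81 | 0.808 | 0.704 |

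With 36 completers, the d detectable with 80% power in a two-sided 5% test is 0.96.

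**Step 3: where the two rules disagree.** With 18 per arm, the observed d equals t / √9 = t / 3.
- One-sided significance needs an observed d above 1.691 / 3 = 0.564.
- The 95% interval excludes zero on the benefit side only if the observed d exceeds 2.032 / 3 = 0.677.
- Between 0.564 and 0.677 the one-sided P value is below 0.05 and the 95% interval includes zero. If d = 0.85 is true, the probability of this is 0.803 − 0.698, or about 0.106.

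**Step 4: would baseline adjustment restore the power?** The documents give no correlation r between baseline and follow-up, so r is an assumption here. If 0.85 is the effect on the change score, adjusting for baseline multiplies the residual variance by (1 + r)/2, so the effective d is 0.85 / √((1 + r)/2), with 33 degrees of freedom. Two-sided power with 36 completers:

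| Assumed r | Effective d | Power |
|---|---|---|
| 0.5 | 0.98 | 0.82 |
| 0.7 | 0.92 | 0.77 |
| 0.8 | 0.90 | 0.74 |
| 0.9 | 0.87 | 0.72 |

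**The case against.** The best defence is that the plan is one-sided throughout. The hypothesis is directional, the sample size is openly tied to that direction, and P ≤ 0.05 is silent on sidedness. On this view the 95% interval is a reporting format and the 80% stands. Much of this is fair. The figure of 36 is correct for the test it assumes, and nothing in the document says the test is two-sided. A reader might infer that the trial simply has 70% power, but the document does not support that as an unconditional statement. It holds if the test is two-sided and 10% drop out, a rate the protocol itself calls conservative. Nor can a software default for P values settle what was planned.

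The defence does not remove the mismatch. A directional hypothesis is not a declared one-sided test, and if one is meant, the stated interval does not correspond to it. A separate analysis plan might state the sidedness. Even so, the protocol has already fixed both the basis of the sample size and the interval and threshold, and these do not agree.

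Three further inferences should be resisted:
- The printed β = 0.80 would literally mean 20% power, but it is plainly a labelling slip. The 36 reproduces with power 0.80.
- Setting d at 0.85 rather than 0.81 may be optimistic, but it is disclosed with a reason and is no evidence on sidedness.
- Baseline adjustment cannot be assumed to recover most of the lost power. It would at r = 0.5, but at r = 0.8 or above it recovers less than half of the gap between 0.698 and 0.803.

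**Conclusion.** The concern holds as an internal inconsistency between the Sample size and Statistical analysis sections. It is not an arithmetic error, since 36 and 40 both reproduce.

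- **If the primary test is two-sided**, as the 95% interval implies, power at d = 0.85 is about 70% with 36 completers and about 75% with 40. The risk of missing the assumed effect is 25% to 30%, not 20%.
- **If it is one-sided**, power is 80% with 36 and 84% with 40, but the interval can contradict the test on the primary outcome, with probability about 11% at d = 0.85 and 36 completers.

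Either reading needs a correction, because the protocol leaves open which rule makes the primary outcome positive. The figures assume equal arms and a two-sample t comparison of change scores with d = 0.85 on that scale.

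**What to change.** Before unblinding, state the sidedness of the primary test and give the interval that matches it.

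- **Preferred:** a two-sided 5% test with the 95% confidence interval. Restate the power at d = 0.85 as about 70% with 36 completers and 75% with 40, and give the detectable d of 0.96 at 80% power with 36.
- **Alternative:** a one-sided 5% test, declared explicitly, with the matching one-sided bound (the relevant limit of a 90% interval). The stated 80% can then stay.

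In both cases, replace β = 0.80 with power = 0.80 (β = 0.20). If baseline adjustment is cited as improving power, show the assumed correlation and a range.

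The cost is wording in the protocol, in any analysis plan and in the registry entry. The preferred route also means publishing a less favourable power figure. The trial need not be enlarged.

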### Participants and recruitment

Recruitment for this project commenced in December of 2023 and formal data collection began in January of 2024. We anticipate that recruitment will continue until July of 2025 and data collection until September of 2025. Both males and females of diverse races and ethnicities, who live in Preston and its surrounding areas, will be recruited. Recruiting materials will be placed using public patient bulletin boards as well as using social media. Individuals expressing interest in participation were provided with the chance to reach out to the research team for additional details about the study and to address any questions related to participation. Written informed consent will be acquired from all participants.

### Dietary intervention

After the conclusion of their baseline data collection session, participants will be provided with either pure peppermint oil (Piping Rock Health, UK) or placebo. Participants randomized to the peppermint arm will be required to consume 50 µ L of supplement diluted into 100 mL of water twice daily: once in the morning and again in the evening [16,17]. The placebo condition will involve the consumption of a peppermint flavoured cordial (Schweppes, Schweppes Geneva) in the same quantity and manner as the peppermint group. The placebo is the same colour as the peppermint supplement, without the presence of peppermint. To ensure effective blinding, identical opaque 15 mL dropper bottles without any labels, will be supplied to participants in both the placebo and peppermint trial groups, with the only difference being the solution, i.e., placebo or peppermint that they contain. This method of placebo preparation has been shown by previous analyses to provide an effective blinding strategy [16,21]. Additionally, all supplements will be prepared by an independent researcher to maintain blinding, ensuring that the trial researchers are also unaware of the participants’ allocations.

Throughout the study, the participants will be encouraged to maintain their habitual diet and exercise routines; and asked to refrain from consuming any other peppermint supplements. Participants will also be asked to keep a 4-day diet diary prior to the baseline assessment and before the follow-up examination at the end of the 20-day treatment period [19]. This will ensure that there are no differences in dietary patterns between groups and that participants have not made significant changes to their nutritional approach that could influence the study outcomes. For their post-intervention data collection session, all participants will be asked to return any un-used supplementation/ placebo to the laboratory in order to determine the % compliance in each group. Furthermore, in order to examine blinding efficacy, each participant will be asked to which trial arm that they felt that they had been allocated to at the conclusion of their post-intervention data collection session. Participants displaying any adverse events will be discontinued from the study at the earliest opportunity and in both groups loss to follow up will be monitored, as will be any adverse events.

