### Data collection

#### Laboratory visit data.

All measurements will be made at University of Central Lancashire’s physiology and nutrition laboratories and will be undertaken in an identical manner on two occasions, i.e., baseline and post-intervention. The laboratories housed by the University of Central Lancashire are fully accredited by the British Association for Sport & Exercise Sciences, illustrating that they have undergone meticulous inspection and evidenced that; all instrumentation is well maintained in terms of reliability, validity and routine servicing, staff have the appropriate professional and vocational qualifications and that the requisite operational procedures for health and safety are met.

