### Safety reporting

The Sponsor’s Adverse Event Reporting Procedures shall be followed for reporting adverse events. The clinical co-investigator will be in charge of assessing the cause and severity of adverse events, as well as ensuring that appropriate action is done. Data on adverse events will be gathered from the start of any study-related procedure (i.e., upon acquisition of written consent). The participant’s final trial contact will mark the end of the adverse event reporting period.

Throughout the study, we will closely monitor and document both significant and non-serious adverse effects that may be associated with participation in the research or lead to withdrawal from the or study. Serious adverse events encompass any unfavourable medical event. In the event of any necessary modifications to the experimental protocol, we will promptly inform the study ethics committee for re-evaluation and approval, and the trial registry will be updated accordingly. During this period, data collection will be temporarily halted. Non-serious incidents, on the other hand, encompass medical occurrences that do not meet the criteria for serious adverse events.

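### Removing everyone with any adverse event from the study means no day-20 blood pressure for those removed early, which undercuts the declared intention-to-treat analysis

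*Protocol article*

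**What the plan says.** The Dietary intervention section states: "Participants displaying any adverse events will be discontinued from the study at the earliest opportunity". The same sentence then says that losses to follow-up and adverse events will be monitored in both groups. The article does not provide for an SBP reading at exit or at day 20 after such a removal.

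The Statistical analysis section states: "All analyses of the intervention-based data will follow an intention-to-treat approach". Its model compares arms on the change score: "differences in the changes from baseline to 20-days between the two trial arms will be examined using linear mixed-effects models". The primary outcome in Study design and setting matches this: "the primary outcome measure will be the between-group difference in systolic blood pressure from baseline to post-intervention".

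Under Laboratory visit data, measurements "will be undertaken in an identical manner on two occasions, i.e., baseline and post-intervention". No interim visit is described.

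Safety reporting makes the clinical co-investigator "in charge of assessing the cause and severity of adverse events, as well as ensuring that appropriate action is done". It covers non-serious as well as serious events.

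**The concern.** The rule is triggered by any event, however mild and whatever its cause, and its consequence is leaving the study. Stopping a product and stopping follow-up are different decisions, and the sentence merges them. Safety may call for the first. It does not call for skipping a seated cuff reading at a visit already planned.

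The trial has one post-baseline measurement, so removal before day 20 leaves no change score and no intermediate value to use in its place. The participants with a measured outcome are then selected by something that happens after randomisation. One arm takes peppermint oil and the other a flavoured cordial, so events, and hence removals, could be unequal between arms and could be related to response. Randomisation would no longer protect the SBP comparison. An analysis plan can model missing values under assumptions that cannot be tested. It cannot recover readings that the protocol itself prevents.

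**Working it through.** **Tracing one participant.** A mild event is reported on, say, day 8. The Dietary intervention rule removes that participant from the study. The next measurement would have been the post-intervention visit, which no longer takes place. The response in the Statistical analysis model is the change to day 20, with group as the fixed factor, so this participant contributes nothing to the primary comparison. An event first noted at the day-20 visit need not cost the outcome.

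**Reproducing the plan's sample size.** The inputs, from the Sample size section, are d = 0.85, α = 5%, target power 0.80 and a directional hypothesis, read as one-sided. Power comes from the noncentral t distribution with df = n₁ + n₂ − 2 and noncentrality d·√(n₁n₂/(n₁ + n₂)).

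- 18 v 18: noncentrality 0.85 × √(324/36) = 2.55, df = 34, power 0.803. This gives the stated 36.
- 36/(1 − 0.10) = 40, the stated total, so 4 losses are allowed for.

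**Power when removals fall in the peppermint arm only** (d = 0.85, one-sided 5%):

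| Measured, peppermint v placebo | Noncentrality | Power |
|---|---|---|
| 20 v 20 | 2.688 | 0.840 |
| 18 v 20 | 2.616 | 0.822 |
| 16 v 20 | 2.534 | 0.799 |
| 14 v 20 | 2.439 | 0.771 |

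**Chance of using up the allowance.** If each of 40 participants independently has probability q of an event before day 20, the chance of more than 4 removals is 0.05 at q = 5%, 0.37 at 10%, 0.74 at 15% and 0.92 at 20%. These q are assumptions, because the article gives no rate.

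**Distortion of the estimate.** Let p be the share of the peppermint arm removed, and let k be the effect those participants would have shown relative to the rest (k = 1 means the same). With no removals in the placebo arm, the ratio of the completer effect to the intention-to-treat effect is 1/((1 − p) + p·k).

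| p (of 20) | k = 0 | k = 0.5 | k = 1 | k = 1.5 |
|---|---|---|---|---|
| 10% (2) | 1/0.90 = 1.11 | 1/0.95 = 1.05 | 1.00 | 1/1.05 = 0.95 |
| 20% (4) | 1/0.80 = 1.25 | 1/0.90 = 1.11 | 1.00 | 1/1.10 = 0.91 |
| 30% (6) | 1/0.70 = 1.43 | 1/0.85 = 1.18 | 1.00 | 1/1.15 = 0.87 |

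Both p and k are assumed. The 10% row uses the same rate as the plan's dropout allowance.

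**The case against.** **The wording may be looser than it looks.** Safety reporting refers to effects that may lead to withdrawal, which suggests that not every event does. The removal sentence sits in a section about the supplement, so leaving the study might be shorthand for stopping the product. The article also condenses a fuller protocol. This shows that the two sections do not fit together well. It does not override a rule that covers any event, and it does not supply a day-20 reading. Staff who follow the sentence as printed would lose outcomes.

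**Missing outcomes do not in themselves contradict intention-to-treat.** Their handling belongs in an analysis plan that is not shown. That is true of losses the trial cannot avoid. Here the protocol's own rule creates the loss.

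**The effect may be small.** With no interim visit described, removal depends on a participant reporting an event within 20 days. Nothing in the article supports 20% or 30% removal, and the scenarios put every removal in one arm. At 10% removal and k = 0, the shift is 0.85 − 0.85 × 0.9 = 0.085 SD, against a standard error of about √(2/20) = 0.32 SD, so roughly a quarter of one standard error. This stands, and it limits what can be claimed about size.

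**Part of the gap is a choice of estimand.** If the response is weaker because the product was stopped, the completer figure is nearer an on-treatment effect, and measuring everyone dilutes the estimate. That also stands. It is the price of the intention-to-treat effect that the plan says it wants.

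**Conclusion.** The concern holds. Followed as written, the rule leaves participants removed before day 20 without a primary outcome, so the SBP comparison would rest on those free of an earlier adverse event and not on all randomised participants. This follows from the text and needs no assumption.

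The consequence is less certain. The direction of any bias is unknown, and there is none if those removed would have responded like the rest. At an assumed 10% removal in the peppermint arm, the estimate moves by −5% to +11%. Larger distortions, up to +43%, need 6 of 20 removed with no effect at all. Power falls only modestly, from 0.84 to 0.80 with 4 removed or 0.77 with 6 removed, on the plan's one-sided basis at d = 0.85. The 10% dropout allowance protects the number analysed but not the comparability of the arms. The rule should be corrected, because the harm is avoidable and the correction is small.

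**What to change.** Replace the removal sentence in Dietary intervention with wording to this effect:

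> An adverse event may lead to stopping the supplement on the clinical co-investigator's judgement. Every randomised participant who has not withdrawn consent will be asked to attend the day-20 visit, will have SBP measured, and will be analysed in the allocated arm.

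Report the reason for each missing day-20 SBP, by arm. The stopping decision then rests with the role that Safety reporting already charges with judging cause, severity and action.

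**Cost.** There is no new visit and no change to the 36 evaluable or 40 randomised. Safety reporting does attach a procedure to protocol changes: "we will promptly inform the study ethics committee for re-evaluation and approval, and the trial registry will be updated accordingly", with data collection paused meanwhile. Data collection began in January 2024, so outcomes already lost by participants past day 20 cannot be recovered. For them, only reporting by arm and reason remains.

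Some day-20 values will be off product, which lowers power for the intention-to-treat effect. With 20 v 20 measured, an unchanged SD and 20% of the peppermint arm stopping:

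- keeping half the effect: d = 0.85 × (0.8 + 0.2 × 0.5) = 0.765, power 0.77;
- keeping none: d = 0.85 × 0.8 = 0.68, power 0.68.

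Both compare with 0.84 when nobody stops.
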